### Statistical analysis

The primary haemoglobin outcome (measured using a Medonic haematology analyser in the laboratory) at day 84 will be tested for non-inferiority by performing a per-protocol analysis with a 5 % significance level, adjusted using the Bonferroni correction to account for three main comparisons. We will also repeat the main analysis using the intention-to-treat population as a confirmatory analysis.

Secondary outcome analysis of continuous variables (ferritin, sTfR, transferrin, TSAT, CRP, AGP, calprotectin, *ex-vivo* growth, gut microbiota, number of weeks supplemented) will be done using mixed-effect models with individuals treated as a random effect, and secondary outcome analysis of categorical variables (anaemia, ID and IDA) will be modelled using mixed-effect logistic regression. Interactions between study arm and time in the study will be investigated.

Morbidity data will be analysed using mixed-effect models controlled for possible confounders.

Exploratory analysis will be performed using serum iron.

All data will be analysed using Stata v12.1 (StataCorp, LP, USE, http://www.stata.com) and statistical significance will be defined as *p* < 0.05, unless stated otherwise.

In the sub-study, the linear regression of log^57^A^t^ (^57^A^t^ = abundance at time t) against time will be calculated for each subject belonging to the three different groups for the period of Day 0 to Day 84 (with a midpoint sample at day 49). The slope (k_abs_) of the regression reflects the absorption of iron per unit of time. The difference in the slopes between the groups will be equivalent to the average iron absorption over time in each group (k_abs_ in groups A, B, and C, respectively).

The assumption of homogenous labelling will be assessed by testing the linearity of the slope between Days 0, 49 and 84. In each subject, k_abs,i_ will be calculated from the slope of the isotopic ratio decrease over the intervention period. k_abs,c_ will also be calculated for the control period (Day 84 and 168). k_abs_ will be modelled using linear mixed models with time (intervention and control period) and treatment as fixed factors and subjects ID as random factors. The time treatment interaction on k_abs_ will be assessed. A similar but separate analysis will be conducted on the total amount of iron absorbed, which will be estimated from the k_abs_ value in each subject, and the group and time effect will be modelled with linear mixed models. The models will be compared to the standard treatment of supplementation with 12 mg iron/day universal.

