### Recruitment, enrolment and randomisation

A summary chart of all study procedures is illustrated in Fig. 1. Mothers/Guardians of the young children identified during child welfare clinics at the selected health centres will be visited at home where the study will be clearly explained. Demographic information will be collected once the child’s mother/guardian has signed the informed consent form. If the inclusion criteria are met, the child will be invited for further eligibility screening during which they will be physically examined. Height, weight, head circumference, mid-upper arm circumference and triceps skinfold thickness will be measured and a finger prick blood sample for Hb and rapid diagnostic test (RDT) for malaria will be taken. If Hb is ≥ 7 and < 11 g/dL, and the RDT is negative, a venous blood sample of 5 mL will be collected. The mother will then be asked to collect a stool sample from the child within the next two days. Enrolled children will be randomized to one of the three study arms (equal number in each arm) using a block randomization, balanced by Hb concentration and age, to minimise potential baseline imbalance.

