### Laboratory evaluations

#### Blood samples

In the *venous blood samples* collected on Days 0, 49 and 84 the following parameters will be assessed: full haematology panel (using a Medonic M^20M^ GP); ferritin, soluble transferrin receptor (sTfR), serum iron, transferrin, transferrin saturation (TSAT), c-reactive protein (CRP), alpha 1-acid glycoprotein (AGP) (using a fully automated biochemistry analyser Cobas Integra 400 plus); and hepcidin (using the Hepcidin-25 (human) EIA Kit (Bachem) and a Thermo Scientific Multiskan FC Microplate Photometer). Red blood cells (RBCs) will be lysed for measurement of riboflavin status by the erythrocyte glutathione reductase activation coefficient (EGRAC) test.

*Ex vivo* growth of *P. falciparum* will be assessed in washed RBCs using a field-ready 96-well plate method and a basic flow cytometry readout (with the BD Accuri CSampler) in which parasitized RBCs (pRBCs) are identified by DNA dye SYBR green I (Life Technologies). Briefly, cultures will be seeded into RBCs from study participants as rings at 0.5 % initial pRBCs and 1 % haematocrit in triplicate into 96 well plates and maintained for 96 h. Parasite growth rates will be determined by dividing final parasitaemia at 96 h by initial parasitaemia at 0 h [17].

*Ex vivo* growth of sentinel bacteria (*Staphylococcus aureus*, *Staphylococcus epidermidis*, *E. Coli* and *Salmonella* Typhimurium) in participant serum will be assessed by optical density plots confirmed by baseline and end-point colony counts using the cell culture counting facility of a Thermo Scientific Multiskan FC Microplate Photometer [18].

From the Day 0 whole blood samples genotyping for haemoglobinopathies will be done using haemoglobin electrophoresis and DNA will be extracted using the salting out method to look at genetics of iron metabolism. Known genetic risk factors to be assessed include alpha-thalassemia, glucose-6-phosphate dehydrogenase deficiency and sickle traits. Furthermore, putative functional and key tagging variants in iron regulatory and inflammatory pathways will be screened. Much of this will be available from the Illumina Infinium Human Exome Bead Chip (Exome Chip). A specific ‘iron chip’ may be developed.

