### Sample size

This is a non-inferiority trial to evaluate efficacy and the primary endpoint is Hb concentration (measured using a Medonic haematology analyser in the laboratory) at day 84. Based on a SD of 1.15 g/dL of the mean Hb value of children at 24 week of age, from a previous trial conducted at Keneba [19], a sample size of 131 participants in each of the three arms is required using a 1-sided α of 2.5 and a Bonferroni correction to adjust for multiple testing. A total sample size of 393 children followed up for 12 weeks, with a drop-out of less than 15 %, will provide 80 % power to establish that:arm B is non-inferior to arm A on the primary endpoint (Hb concentration at Day 84) defined as the upper 98.3 % confidence limit for the difference in mean Hb being not greater than 0.5 g/dL (non-inferiority margin), the smallest value considered to be of public health relevancearm C is non-inferior to arm A at the same level as abovearm C is non-inferior to arm B at the same level as above

For the sub-study, the power calculation for iron absorption is based on the data from Fomon et al. [20] in infants. Twenty subjects per group are required to resolve a difference in absorbed iron of 0.080 mg/d between the control and intervention period, based on a SD of 0.13 mg/d (paired t-test). The between group difference that we estimate being able to resolve is 0.12 mg/d absorbed iron (unpaired *t*-test). Lower variability is expected in the calculated k_abs_ values, which are independent from Hb, body weight, and iron status, the main contributors to variability in the calculation of iron absorption. Considering attrition due to the long time span of at least 7 months between recruitment (administration of stable isotope dose) and participation in the main study, 30 subjects per group will be recruited.

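### Free improvement: name Day 0 Medonic Hb, age and the balancing strata as covariates for the primary Day 84 Hb comparison, for which the article names none

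*Protocol article*

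**What the plan says.** Under Sample size, the protocol article states that "the primary endpoint is Hb concentration (measured using a Medonic haematology analyser in the laboratory) at day 84". The planning SD is introduced with "Based on a SD of 1.15 g/dL of the mean Hb value of children at 24 week of age", the error rate is set "using a 1-sided α of 2.5 and a Bonferroni correction to adjust for multiple testing", and the criterion is "the upper 98.3 % confidence limit for the difference in mean Hb being not greater than 0.5 g/dL (non-inferiority margin". On this basis "a sample size of 131 participants in each of the three arms is required".

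Under Statistical analysis, the primary Hb outcome "at day 84 will be tested for non-inferiority by performing a per-protocol analysis", with a Bonferroni correction for three comparisons and a repeat in the intention-to-treat population. The only adjustment mentioned there for the primary outcome is for multiplicity. The same section names mixed-effect models for the continuous secondary outcomes, mixed-effect logistic regression for the categorical ones, and confounder control for morbidity.

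Two other places bear on the point. Under Recruitment, enrolment and randomisation, children are allocated "using a block randomization, balanced by Hb concentration and age, to minimise potential baseline imbalance". Under Blood samples, in venous blood "collected on Days 0, 49 and 84 the following parameters will be assessed: full haematology panel", run on the Medonic. A baseline value on the endpoint's own scale is therefore available for the enrolled children.

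**The concern.** Allocation is balanced on two factors that the investigators evidently expect to predict the outcome, but the primary comparison as described does not use them. Balancing removes part of the chance variation between arms. An analysis that ignores the balancing factors still counts that variation in its standard error, so the interval is too wide for the design. Leaving baseline Hb out also leaves the variance it explains in the residual.

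Non-inferiority is decided by where one confidence limit falls relative to 0.5 g/dL. Unneeded width therefore makes it harder to show non-inferiority when it is true. What is at stake is efficiency and the calibration of the interval, obtainable from data already being collected.

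**Working it through.** **Inputs from the article.** SD 1.15 g/dL; margin 0.5 g/dL; one-sided 2.5 % divided by 3 = 0.00833 per comparison (z = 2.394), which is the two-sided 98.3 % interval; 80 % power (z = 0.842); drop-out 15 %, the upper bound stated; 131 per arm.

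**Assumptions not in the article.** True difference of zero. Multiple correlation r between Day 84 Hb and the covariates within arm, varied from 0 to 0.5.

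**Step 1: reproduce the stated sample size.**
n = 2 × SD² × (2.394 + 0.842)² / margin² = 2 × 1.3225 × 10.47 / 0.25 ≈ 110.8, so 111 evaluable per arm. Then 111 / 0.85 = 130.6, so 131 per arm and 393 in total. This matches the article exactly. One-sided 0.05/3 gives 94 (111 after drop-out), and one-sided 0.025 without Bonferroni gives 84 (99 after drop-out); neither matches. The figure was therefore planned on the raw SD with no allowance for covariates.

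**Step 2: effect of adjustment at 111 evaluable per arm.**
Residual SD = 1.15 × √(1 − r²). Half-width = 2.394 × residual SD × √(2/111). Power = Φ(0.5 / [residual SD × √(2/111)] − 2.394).

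| Assumed r | Residual SD (g/dL) | 98.3 % CI half-width (g/dL) | Power per comparison |
|---|---|---|---|
| 0 | 1.150 | 0.370 | 80.1 % |
| 0.2 | 1.127 | 0.362 | 81.9 % |
| 0.3 | 1.097 | 0.353 | 84.2 % |
| 0.4 | 1.054 | 0.339 | 87.3 % |
| 0.5 | 0.996 | 0.320 | 91.1 % |

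**Step 3: what balancing does to an unadjusted test.** A simulation used two arms of 111, allocation balanced within six strata of baseline Hb, and 15,000 runs per cell. Size is the rejection rate when the true difference equals the margin (nominal 0.0083).

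| Assumed r | Size, unadjusted | Size, ANCOVA | Power, unadjusted | Power, ANCOVA |
|---|---|---|---|---|
| 0 | 0.0076 | 0.0077 | 79.5 % | 79.5 % |
| 0.3 | 0.0065 | 0.0089 | 80.2 % | 83.3 % |
| 0.5 | 0.0026 | 0.0077 | 82.3 % | 90.4 % |

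The Monte Carlo standard error of a size near 0.0083 is √(0.0083 × 0.9917 / 15,000) ≈ 0.0007. ANCOVA is thus compatible with nominal throughout, while the unadjusted test becomes conservative as r rises. The net gain under balanced allocation is about 3 points at r = 0.3 and 8 points at r = 0.5. This is slightly less than Step 2 suggests, because balancing alone already helps the unadjusted test a little. The simulation takes the balancing Hb and the covariate to be the same measurement.

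**The case against.** The strongest objection is that the article never says the primary comparison is unadjusted. It names no model, and a covariate list is something an article may leave to the full protocol or SAP, which are not shown. Planning on the raw SD is a common cautious choice when the baseline correlation is unknown, and a difference in means may be an adjusted one. This stands: a reader might infer that the investigators have settled on an unadjusted test, and the text does not support that. What remains is that the criterion as written is a difference in mean Hb planned on the raw SD, and that the section gives models or confounder control for secondary and morbidity outcomes but nothing comparable for the primary one. Followed as written, it would not use its own balancing factors.

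Second, no error rate is endangered. A conservative test does not raise the chance of a false non-inferiority claim. That also stands. A reader might infer that the trial is underpowered or its primary analysis invalid; Step 1 shows that the stated power is right on the stated inputs.

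Third, the size of the gain rests on an assumed r. Entry Hb is confined to 7 to below 11 g/dL, which tends to lower the correlation, and at r = 0.3 the half-width changes by only 0.02 g/dL against a margin of 0.5. This is fair, so large gains should not be promised.

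Fourth, eligibility rests on a finger-prick Hb, the Medonic reading comes from the venous sample drawn afterwards, and the article does not say which one balances the allocation. This too is correct, and the fix must keep the two apart.

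A reader might also infer that per-protocol exclusions will upset the Hb balance. The article gives no figures to show that. Adjustment would deal only with imbalance in the measured covariates, not with selection in general.

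**Conclusion.** The point holds as a free improvement, not as the correction of an error. If the primary comparison is made as the article describes it, with no covariates, its interval is wider than a design balanced on Hb and age warrants. The half-width would fall from 0.37 to about 0.35 g/dL at r = 0.3, or 0.32 g/dL at r = 0.5, and power per comparison would rise from 80 % to about 84 % or 91 %. These figures assume 111 evaluable children per arm, an SD of 1.15 g/dL, a true difference of zero, and a correlation that the documents do not supply. The lower end of the range is the more likely. At r = 0 the loss is negligible.

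**What to change.** In the Statistical analysis section, or in the SAP before unblinding, specify the primary analysis as an ANCOVA of Day 84 Medonic Hb on arm, Day 0 venous Medonic Hb and age, both continuous, plus the balancing strata actually used. State whether those strata rest on finger-prick or venous Hb. Take all three non-inferiority contrasts and their 98.3 % limits from this model, in both the per-protocol and intention-to-treat sets, and report the unadjusted comparison as a sensitivity analysis. If the SAP already says this, confirming it is enough.

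The cost is one or two sentences. No measurement, visit or sample is added, and the sample size need not change.

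### Plain Bonferroni over the three non-inferiority tests is valid and meets the stated 80 % per comparison, but Holm's step-down test gives more power at the same family-wise one-sided 2.5 %

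*Protocol article*

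**What the plan says.** The Sample size section of the protocol article names the endpoint: "the primary endpoint is Hb concentration (measured using a Medonic haematology analyser in the laboratory) at day 84". It sizes the trial "using a 1-sided α of 2.5 and a Bonferroni correction to adjust for multiple testing"; the unit is missing, and 2.5 % is plainly meant. The planning value is "Based on a SD of 1.15 g/dL of the mean Hb value of children", and the result is that "a sample size of 131 participants in each of the three arms is required", "with a drop-out of less than 15" per cent. This number "will provide 80 % power to establish that" three listed conclusions: B is non-inferior to A, C to A, and C to B. Each is decided by the "upper 98.3 % confidence limit for the difference in mean Hb being not greater than 0.5 g/dL (non-inferiority margin"), and all three are held to the same level.

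The Statistical analysis section repeats the choice. The primary test is per protocol at 5 %, "adjusted using the Bonferroni correction to account for three main comparisons", with an intention-to-treat repeat as confirmation. No step-down or other sequential rule is mentioned in either section.

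The Study objectives section words the primary objective as whether the three regimens are all non-inferior.

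**The concern.** Single-step Bonferroni holds every comparison at one-sided 0.833 %, whatever the other two show. Holm starts at the same 0.833 % for the smallest p-value and relaxes to 1.25 % and then 2.5 % as claims succeed. It controls the family-wise error under any dependence between the tests, so the shared arms cause no difficulty, and it needs no extra assumption. Every claim that Bonferroni makes, Holm makes too.

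The gain is largest when several claims are wanted together, and both the list of three conclusions and the wording of the objective point that way. At stake is power that could be had without another child or another sample. The error rate is not in question.

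**Working it through.** **Inputs.** From the Sample size section: margin δ = 0.5 g/dL, SD σ = 1.15 g/dL, family-wise one-sided α = 0.025 over three tests, power 80 %, loss up to 15 %. From the recruitment section: equal arms. Assumption: true difference 0. The article states none, but 0 reproduces its sample size.

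**Reproducing the plan's number.**
- Level per test: 0.025 / 3 = 0.00833, z = 2.394. For 80 % power, z = 0.842.
- n = 2σ²(2.394 + 0.842)² / δ² = 2 × 1.3225 × 10.47 / 0.25 = 110.8, so 111 evaluable per arm.
- 111 / 0.85 = 130.6, so 131 enrolled per arm and 393 in total, as stated.
- Power at 111: the standard error is 1.15 × √(2/111) = 0.1544. Then 0.5 / 0.1544 − 2.394 = 0.845, which gives 80.1 %.

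The stated 80 % is therefore the power of each comparison taken singly at the Bonferroni level. The 98.3 % limit fits this when read as two-sided (1 − 0.05/3 = 98.33 %, leaving 0.833 % in each tail). Read as a one-sided limit, it would need only 94 evaluable and 111 enrolled per arm, which is not the stated number.

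**Bonferroni against Holm.** One million simulated sets of three arm means, SD treated as known, with the correlation between contrasts arising from the shared arms. Bonferroni tests each p-value at 0.00833. Holm tests the ordered p-values at 0.00833, 0.0125 and 0.025, stopping at the first failure.

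| True difference 0 | Bonferroni | Holm |
|---|---|---|
| 111 per arm: each comparison | 80.1 % | 86.3-87.9 % |
| 111 per arm: B and C both against A | 68.9 % | 80.7 % |
| 111 per arm: all three | 57.6 % | 75.1 % |
| 111 per arm: at least one | 99.2 % | 99.2 % |
| 131 per arm (no loss): all three | 70.3 % | 84.5 % |

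The gain for all three is 75.1 − 57.6 = 17.5 points at 111 per arm and 84.5 − 70.3 = 14.2 points at 131. No Bonferroni rejection was lost in any run. In the boundary configurations tried, Holm's simulated family-wise error was at most 0.0248.

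**Sensitivity of the all-three figure at 111 per arm.**
- B and C both 0.1 g/dL below A: 35.8 % to 54.3 %.
- C alone 0.2 g/dL lower: 15.8 % to 29.2 %.
- B 0.1 and C 0.2 g/dL lower: 19.2 % to 34.3 %.
- True difference 0, with 98.3 % read as a one-sided limit: 69.6 % to 85.3 %.

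The gain is thus about 13 to 19 points across these settings.

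**If all three must succeed together.** This is an intersection-union test. Each comparison is tested at one-sided 2.5 % without adjustment, and at 111 per arm with true difference 0 the power is 76.4 %, slightly above Holm.

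**The case against.** The strongest defence is that nothing in the plan is wrong. Bonferroni is valid, is used consistently for sizing and analysis, and delivers the stated power. That stands: this is lost efficiency, not an error-rate fault.

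A second objection also stands. The plan decides by confidence limits, and Bonferroni limits give simultaneous coverage that agrees with every decision. Holm matches Bonferroni on the family-wise error of the tests only and has no equally simple matching intervals. Every claim it adds has a 98.33 % limit beyond 0.5 g/dL. The whole 17.5-point joint gain consists of trials with at least one such claim. Changing only the phrase in the Statistical analysis section would therefore contradict the rule in the Sample size section.

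Third, the size depends on what counts as success. If the claims are separate, as the Sample size section lists them, the gain is 6 to 8 points per claim and nothing for at least one success. If they are required jointly, no adjustment is needed at all. On neither reading, however, does plain Bonferroni give the most powerful valid test.

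A reader might infer that the trial promises 80 % for all three claims together and falls short. The article does not support this: its figure introduces a list of three conclusions, and the number of children reproduces 80 % for each one. A reader might also take the 17 points as a general figure. It holds for joint success only, at the full 15 % loss and zero true difference, whereas the article expects less than 15 % loss.

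**Conclusion.** The point holds as a cheap improvement. For the tests themselves, plain Bonferroni is less powerful than Holm at equal family-wise one-sided 2.5 %, and what it offers in return is agreement between the intervals and the decisions. With SD 1.15 g/dL and no true difference, the gain is 6 to 8 points per comparison at 111 evaluable per arm. For all three claims it is 17.5 points at 111 per arm and 14.2 points at 131. Holm does not bring all-three power to 80 % at 111 per arm, and it does not change the chance of at least one success.

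**What to change.** Before unblinding:

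1. In the Statistical analysis section, replace the Bonferroni correction with Holm's step-down procedure on the three one-sided non-inferiority p-values (0.833 %, 1.25 %, 2.5 % in order; family-wise one-sided 2.5 %).
2. In the Sample size section, reword the decision rule so that non-inferiority is declared when the Holm-adjusted one-sided p-value is at most 0.025. Report the two-sided 98.33 % intervals beside it as descriptive simultaneous intervals, and say that they need not match every decision.
3. State whether the objective is three separate claims or one joint claim. If it is strictly joint, specify an intersection-union test at one-sided 2.5 % each in place of Holm.

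The cost is wording in two sections, with no change to the number of children or the data collected. The Bonferroni-based sample size can stand as a conservative basis. The price is in presentation: a claim that Holm adds will appear beside a 98.33 % limit beyond 0.5 g/dL, so the adjusted p-value must be shown with it and the difference explained.

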### Study objectives

The *primary objective* is to evaluate whether weekly hepcidin-based screen-and-treat at 12 mg iron/day, screen-and-treat at 6 mg iron/day and 12 mg iron/day universal supplementation for 12 weeks are all non-inferior. The primary endpoint is Hb (measured using a Medonic haematology analyser in the laboratory) at day 84. Secondary endpoints related to the primary objectives are:i)Proportion of anaemia (Hb < 11 g/dL) at Day 84;ii)Proportion of iron deficiency (sTfR/logFerritin ratio > 3.2 or > 2.0 in the presence of inflammation (CRP > 5 mg/L) and ferritin < 12 μg/L or < 30 μg/L in the presence of inflammation) at Day 84;iii)Proportion of iron deficiency anaemia (Hb < 11 g/dL and sTfR/logFerritin ratio > 3.2 or > 2.0 in the presence of inflammation and ferritin < 12 μg/L or < 30 μg/L in the presence of inflammation) at Day 84;iv)Ferritin (only participants without inflammation), soluble transferrin receptor (sTfR), transferrin and transferrin saturation (TSAT) at Day 84.

The *secondary objectives* are the evaluation of i) the feasibility of adopting a hepcidin-based screen-and-treat approach to iron supplementation in young children (number of weeks supplemented with iron); ii) beneficial effects with screen-and-treat with respect to maternal reporting of child illness and safety indices (inflammatory and immune activation markers, faecal gut inflammation markers, gut microbiota, *ex-vivo* bacterial and *P. falciparum* growth); and iii) overall iron absorption over the 12 week supplementation period in the three study arms (sub-study).

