## Methods/design

This paper describes the methodology of a randomized controlled non-inferiority trial comparing three different arms. Two arms are screen-and-treat approaches using hepcidin to indicate whether the body is ready to absorb iron and thus making it safe to give iron and the third arm is universal iron supplementation (recommended by WHO in non-malarial areas). Children randomized to the universal arm will get 12 mg iron daily for 12 weeks and children randomized to the screen-and-treat groups will receive 12 mg or 6 mg iron daily if their weekly hepcidin indicates a low value (<5.5 ng/mL), or 0 mg iron if their hepcidin indicates a high value (≥5.5 ng/mL) for the next seven days for a total of 12 weeks.

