### Study design

This is a proof-of-concept, three-arm, double-blind randomized controlled non-inferiority trial. The three arms are:A)Supplementation with a MNP containing 12 mg iron dailyB)Supplementation with a MNP containing 12 mg iron/day if hepcidin is below 5.5 ng/mL, or MNP containing 0 mg iron/day if hepcidin is ≥ 5.5 ng/mL, based on a weekly hepcidin screening indicating whether iron can be given for the next 7 daysC)Supplementation with a MNP containing 6 mg iron/day if hepcidin is below 5.5 ng/mL, or MNP containing 0 mg iron/day if hepcidin is ≥ 5.5 ng/mL, based on a weekly hepcidin screening indicating whether iron can be given for the next 7 days

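### Weeks of iron is one total per child and fixed at 12 in arm A, so the mixed model assigned to it cannot be estimated, and a variance pooled over three arms can misstate its standard errors

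*Protocol article*

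**What the plan says.** Study objectives (protocol article) gives one measure for the feasibility objective: "number of weeks supplemented with iron".

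Statistical analysis places that outcome last in a list of continuous variables, after laboratory, stool and ex-vivo measures taken at several visits, and assigns the whole list one method: "gut microbiota, number of weeks supplemented) will be done using mixed-effect models with individuals treated as a random effect". It adds: "Interactions between study arm and time in the study will be investigated". Logistic mixed models are reserved for anaemia, iron deficiency and iron deficiency anaemia. Outside the primary analysis, "statistical significance will be defined as *p* < 0.05" unless stated otherwise.

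Methods/design fixes the exposure in the reference arm: "Children randomized to the universal arm will get 12 mg iron daily for 12 weeks". In arms B and C the iron content is decided week by week, "based on a weekly hepcidin screening indicating whether iron can be given for the next 7 days".

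The article makes no exception for this outcome, defines no repeated version of it, and does not say how arm A enters its analysis.

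**The concern.** Two features of the outcome do not fit the assigned model.

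- **One value per child.** A random effect for the child is separable from residual error only if a child contributes more than one observation. A total over 12 weeks has no time dimension either, so it cannot carry an arm-by-time interaction.
- **No variance in arm A.** Apart from drop-out or missed supply, every child there scores 12. A normal model with one residual variance averages this zero with the real variance in B and C, and applies the average to every contrast.

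At stake is the precision attached to the feasibility result. B versus C is the only between-arm contrast in which both sides are measured. A contrast of B or C with A sets an observed mean against a constant chosen by the protocol. Its estimate (weeks saved) is useful, but a p-value for fewer weeks than universal supplementation says little about feasibility.

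**Working it through.** **Inputs from the protocol article.** Sample size: 131 per arm, SD 1.15 g/dL, margin 0.5 g/dL, one-sided 2.5 % with Bonferroni correction over three comparisons, 80 % power, drop-out below 15 %. Methods/design: arm A has 12 of 12 weeks on iron. Statistical analysis: p < 0.05, taken as two-sided. No mean or SD for weeks on iron is given, so those below are assumptions.

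**Step 1: the number per arm.** One-sided α = 0.025/3 = 0.00833, so z = 2.394; for 80 % power z = 0.842. Then n = 2 × [1.15 × (2.394 + 0.842)/0.5]² = 110.8, rounded up to 111, and 111/0.85 = 130.6, rounded up to 131. This reproduces the stated figure and gives 111 completers per arm.

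**Step 2: the random effect.** With one value per child, the variance of an observation is τ² + σ², and no covariance separates the two parts. For one simulated data set, the log-likelihood was −806.64 whether the random intercept took 0, 25, 50, 75 or 99 % of the variance. Only the sum is estimable, so the model is ordinary three-arm regression. A trial fit (not in Stata, the package the protocol names) recovered that sum but warned that the Hessian was not positive definite.

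**Step 3: pooled variance, completers only.** Let the variances be 0 in A and s² in B and C, with equal n.

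- Pooled variance = (0 + s² + s²)/3 = ⅔s².
- B versus C: the true variance is 2s²/n and the model uses 2(⅔s²)/n. The SE ratio is √(2/3) = 0.816, which is 18 % too small. Type I error = 2[1 − Φ(1.96 × 0.816)] = 10.95 %.
- B or C versus A: the true variance is s²/n and the model uses 2(⅔s²)/n. The SE ratio is √(4/3) = 1.155, about 15 % too large. Coverage of a 95 % interval = 2Φ(1.96 × 1.155) − 1 = 97.6 %.

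These ratios hold for any s² shared by B and C. Simulation (20,000 trials, 111 per arm, assumed means 3.6 to 8.4 weeks, SD about 1.7 to 3.4) gave B-versus-C type I error of 10.8 to 11.2 % under equal means, and coverage against A of 97.5 to 98.1 %. If supply in arm A is slightly imperfect (SD 0.5 or 1, against an assumed 3 in B and C), type I error is 10.7 % or 10.0 %.

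**Step 4: leavers counted with the weeks they received.** Assume a fraction d leaves in every arm, at a week uniform over 0 to 11 (mean 5.5, variance 143/12 = 11.92). Before drop-out, B and C are beta-binomial with mean 6 and SD 2.2 or 3.

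- Variance in A = 11.92d + 6.5²d(1 − d). For d = 0.05 this is 0.60 + 2.01 = 2.60 (SD 1.6); for d = 0.15 it is 1.79 + 5.39 = 7.17 (SD 2.7).
- The same mixture calculation gives a B or C variance of 9.35 (SD 3, d = 0.05) and 6.19 (SD 2.2, d = 0.15).
- SD 3, d = 0.05: pooled variance (2.60 + 2 × 9.35)/3 = 7.10; ratio √(7.10/9.35) = 0.871; type I error 8.8 %.
- SD 2.2, d = 0.15: pooled variance (7.17 + 2 × 6.19)/3 = 6.52; ratio √(6.52/6.19) = 1.026; type I error 4.4 %.

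Simulation with 131 per arm (6,000 runs) gave 7.4 to 8.8 % at 5 % drop-out, 5.7 to 6.8 % at 10 % and 4.6 to 6.6 % at 15 %, in line with these two extremes.

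**Step 5: after the fix.** In the completers' simulation, with B versus C judged on those two arms' own variances, 95 % interval coverage was 94.8 to 95.3 %. For B against the constant 12, as a one-sample interval, it was 94.6 to 94.9 %.

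**The case against.** The best defence is that the article does not commit to the harmful version of the analysis. It does not say that arm A enters the model for this outcome, that one residual variance is used, or that B and C are formally compared on weeks. The feasibility objective concerns the screen-and-treat approach, which exists only in B and C. A full analysis plan may restrict the comparison to those arms or use robust errors, and the distortion would then vanish. The outcome is also secondary, with no hypothesis, threshold or decision rule attached.

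This stands as a limit on the consequence. It does not rescue the model: the article names this outcome and assigns it a method that a per-child total cannot support, which is more than a detail left for later. One could read the endpoint as weekly yes/no data, which would justify a child random effect. The article, however, lists it as continuous and keeps logistic models for other outcomes.

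A reader might infer two stronger things:

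- **That the superfluous random effect itself makes the error bars wrong.** It does not. It is merely unidentifiable; any distortion comes from pooling arm A's variance.
- **That the B-versus-C test will run at 11 %.** That needs arm A at or very near 12, as among completers. The article does not say how leavers are counted, and with partial weeks the inflation is smaller and can disappear.

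**Conclusion.** The point holds as a mismatch between endpoint and model. The child random effect and the arm-by-time interaction cannot be estimated for a single total per child, and what remains is a three-arm regression.

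The effect on precision is conditional on a common residual variance that includes arm A. It then runs both ways: B versus C is anti-conservative, at worst by the completers' figures, and the contrasts with A are conservative. Where leavers keep their partial weeks, the B-versus-C error rate lies at about 5 to 9 % under the assumed drop-out pattern. The sizes for completers rest on equal arm sizes and a shared SD in B and C; those for leavers rest also on the assumed leaving weeks, mean and SDs.

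The estimated mean weeks, the primary haemoglobin analysis and the sample size of 131 per arm are untouched. The correction is worth making because this is the only measure stated for the feasibility objective, but its reach ends there.

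**What to change.** 1. Remove the number of weeks supplemented from the mixed-model list, and state that the arm-by-time interaction does not apply to it.
2. Compare weeks on iron, or the proportion of weeks on iron, between arms B and C only, using those two arms' own variances or robust standard errors.
3. Describe arm A as 12 weeks by design. Report each screening arm's mean weeks saved against 12 with its own confidence interval.
4. State whether children who leave early are counted with the weeks they received or left out, since this changes the result.

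A logistic model of the weekly iron decision in B and C, with a child random effect and week, is optional. It would make proper use of repeated data, but it answers a somewhat different question from the named endpoint.

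The cost is a few lines of analysis-plan wording. The weekly hepcidin results already drive allocation, so no new data are needed.
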